## Abstract

**Background:**

A growing body of evidence suggest an association between physical activity levels and students psychological well-being. A number of research studies have evaluated playground interventions that aim to increase physical activity levels, decrease conflict and bullying, and improve students behaviour. The HAPPY Study will evaluate the success of an intervention combining environmental modifications, teacher development, and peer support that can culminate in an easy to implement, low cost and effective model for increasing physical activity, and improving psychological well-being for children.

**Methods/Design:**

Data will be collected at six New South Wales (NSW) primary schools, on physical activity levels, on-task time during classes, and social support for physical activity during a 12 month Cluster Controlled Trial (CT). Three quantitative data collection tools will be used to capture student’s physical activity levels during lunch and recess breaks (the SOPARC tool), student’s on-task behaviour during classes following recess and lunch breaks (the BOSS tool) and where students receive the most encouragement to be physically active from (the Physical Activity Social Support Scale survey). Baseline data will be analysed against follow-up data, collected after an intervention that is rolled out in all schools as part of a stepped wedge CT design.

**Discussion:**

A review of relevant Australian and New Zealand literature suggests that playground interventions can be successful at increasing physical activity levels, increasing social and conflict resolution skills in students, and decreasing incidences of bullying. This study will investigate any correlation between physical activity levels, and student behaviour during classes following breaks.

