## Background

A multitude of evidence produced from research over the last decade in Australia clearly demonstrates the need for increased physical activity in primary school-aged children [1–3]. There are many health benefits from children being physically active, including greater cardiovascular fitness, lower systolic blood pressure and decreased risk of obesity [1]. Current research suggest that only about half of all Australian primary school aged children are meeting the National Physical Activity recommendations [4] guidelines of 60 min a day of moderate to vigorous physical activity (MVPA) [2].

As well as physical health, being physically active can have behavioural benefits for children, and these benefits to behaviour in primary school students are also becoming increasingly well evidenced [5, 6] and the importance of healthy eating and physical activity has been linked to positive behaviour in classrooms, increased on-task behaviour during class time, and higher levels of social competence [7–11]. The development of many social skills is another psychological benefit children can receive from participating in physical activity during unstructured play time (i.e. recess and lunch breaks. Pellegrini and Blatchford [12] found that social skills such as sharing, negotiation and conflict resolution were fostered through recess and lunchbreak activities.

The Healthy Active Peaceful Playgrounds for Youth (HAPPY) Study, aims to examine the relationship between physical activity and behaviour in primary school students, and to understand the environmental and societal factors that encourage physical activity in primary school students. Physical activity data will be collected before, during, and after the intervention to measure the impact that environmental modifications, social support and teacher training has on physical activity levels. This data collected on students behaviour will be gathered using a survey and direct observations in class time following breaks. Comparison of these data sets should allow for any trends between physical activity, and psychological well-being in students identified and explored.

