### Intervention design

The Peaceful Playgrounds Program is a primary school-based package that uses permanent playground markings, teacher training and accompanying resources to promote physical activity in playgrounds, teach fundamental movement skills, and support social skill development in students. The Peaceful Playgrounds Program will be used in the HAPPY Study as the intervention, and the effects of this on both physical activity levels, and behaviour in students measured.

Several research studies using either the Peaceful Playgrounds Program, or a similar playground based intervention, have shown changing playgrounds in primary schools to be more conducive to play, and supporting school teachers and students to make use of these spaces can significantly increase levels of physical activity, enjoyment of physical activity and improved social interaction skills (i.e. conflict resolution, and sharing) [17–19]. Peaceful Playgrounds will run a multi-component intervention that incorporates elements of environmental, and social intervention, as well as a teacher professional development to increase physical activity participation.

The environmental component of intervention involves the instillation of multi-coloured playground markings that act as visual prompts for students and teachers to be physically active. The markings will be designed specifically for each participating school, and teaching resources will be provided including games, activity suggestions and units of work that can be performed in relation to the markings. Accompanying equipment and play resources will be provided to schools to support engagement with the playground markings and increase physical activity.

Professional learning support will be offered to teachers at participating schools, which will include strategies for initiating play during breaks, games and activities that support the development of social skills in students such as sharing and self-regulation, and methods of supporting conflict resolution for the playground. The teacher training will also include an online network to provide a platform for teacher self-reflection, discussion forums and opportunities to interact with other participating teachers and the research team.

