A Student Ambassador program will be implemented during the intervention to increase the social support students receive to be physically active. Selected students from Stage 3 (years 5 and 6) classes at each school will undertake a student leadership program to develop knowledge and skills to become physical activity ambassadors during break times. The students will be taught techniques from the Peaceful Playgrounds Program to initiate games and encourage social inclusion in their peers.

The Peaceful Playgrounds intervention is expected to increase vigorous physical activity levels in children, encourage participation and enjoyment of physical activity, and structure play in a way that supports socialisation and emotional well-being in children. The HAPPY Study will determine if Peaceful Playgrounds is an effective, efficacious, and scalable intervention.

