### Outcomes

The evaluation of the HAPPY Study will be done using three different quantitative instruments to report on the physical activity levels, students’ behaviour in class, and sources of social support to be physically active. Measurement of these three data sets, will allow the research team to analyse the effects of each component of the intervention; how playground markings can effect physical activity levels during lunch and recess; how this increase, as well as social skills taught through the Peaceful Playgrounds intervention may impact students behaviour during class; and how teacher and student development influences from where, and how frequently students’ receive encouragement to by physically active.

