### Statistical methods

Using the Statistical Package for Social Sciences (SPSS, v21), descriptive statistics and measures of central tendency will be used to describe the effect of the intervention from baseline to follow-up data in each step of the study.

Regression analysis will be completed for this study, to determine genuine relationships between the intervention, and the outcomes for physical activity levels, students’ on-task behaviour time, and frequency of social support for physical activity. Mixed-model ANCOVAs in SPSS will be computed, and each mixed model will be fitted to the data using the restricted maximum likelihood method. Percentage of occurrence (i.e. frequency) data will be analysed using ×2. For each mixed model, sex will be included as fixed effects, with the school included as a random effect to account for the effects of stepping by school. This is a standard statistical procedure for analysis of clustered datasets [27].

Intra-cluster comparisons will be completed between control and intervention periods, and for analyses involving school level characteristics of physical activity, the unit of analysis will be one scan of one area.

If schools decide to stop participating in the study, data pertaining to that school will not be included in the final analyses. Likewise, if a student selected for the behavioural observation component of the study decides to stop participating in the study their data will not be used in the final analyses. For all other components of the study (i.e., physical activity observation and Social Support), intention to treat principles will be followed and all possible data collected will be analysed.

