## Discussion

Physical activity is generally promoted for its well-evidenced positive impact on children’s physical and mental health [28]. However, increased participation in physical activity is also thought to lead to greater of cognitive functioning (information processing), memory, concentration, behaviour and academic achievement for children [29]. The HAPPY Study aims to examine the relationship between physical activity and behavioural well-being in primary school students, and to understand the environmental and societal factors that encourage physical activity in primary school students. This study will measure the Peaceful Playgrounds intervention; whether playground markings increases physical activity levels; if teacher training and a student leadership program encourage students to be more physically active; and whether an increase in physical activity, and social skill development will change students’ behaviour.

The HAPPY study will add to the literature around physical activity in primary schools, the effect physical activity has on behaviour, and whether interventions such as Peaceful Playgrounds successfully impact physical activity and behaviour. Within the physical activity area, the HAPPY Study will provide observational data on physical activity levels in primary school students during recess and lunch breaks. The Peaceful Playgrounds intervention will also provide teachers with resources and training to deliver physical activity sessions outside of the curriculum, so this study will also show the effectiveness of this at increasing physical activity, and encouraging student to be active. While, there is already a large number of studies around effectiveness of playground interventions [13, 14], the Peaceful Playgrounds intervention used in this study is the first we are aware of that combines environmental modifications, teacher development and student leaderships components to influence physical activity levels.

The study will also add to the body of evidence that reports on the effect play (physical activity) can have on children’s socialisation, their creativity, and their behaviour. Currently, there is limited Australian data available on this, and international studies have a focus on academic achievements, rather than the behaviour and on-task time this study will be reporting on.

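### The activity–behaviour association is not separated from the intervention, which may move both variables, so an unadjusted correlation over all periods can be non-zero even if activity has no effect on behaviour

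*Protocol article*

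**What the plan says.** The Background says the study "aims to examine the relationship between physical activity and behaviour in primary school students", and the Discussion repeats this aim. The abstract announces the analysis in one sentence: "This study will investigate any correlation between physical activity levels, and student behaviour during classes following breaks". The Background adds how the link is to be found: "Comparison of these data sets should allow for any trends between physical activity, and psychological well-being in students identified and explored".

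The design is a stepped wedge in which all schools begin as controls and all receive the package (Study Design). Two effects of the package are described:

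- **On activity.** "The Peaceful Playgrounds intervention is expected to increase vigorous physical activity levels in children" (Intervention design).
- **On behaviour, by two routes.** The Outcomes section asks "how this increase, as well as social skills taught through the Peaceful Playgrounds intervention may impact students behaviour during class". The Discussion asks "whether an increase in physical activity, and social skill development will change" behaviour. Teacher training includes "games and activities that support the development of social skills in students such as sharing and self-regulation" (Intervention design).

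The Outcomes section also says that measuring the three data sets will let the team analyse what each component does. The end of the Discussion leaves to later research the question of which parts of the intervention produce which effects.

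Statistical methods describes regressions of each outcome on the intervention: "For each mixed model, sex will be included as fixed effects, with the school included as a random effect". It describes no model of behaviour on activity.

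**The concern.** If the package raises activity through one route and improves classroom behaviour through another, intervention status is a common cause of the two. School-terms under intervention will then tend to be high on both, and control school-terms low on both. A correlation across all of them partly reflects this shared shift and not any effect of activity on behaviour.

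A random effect for school would not remove it, because intervention status changes within each school.

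The relationship is a stated aim. A package that worked on behaviour only through social-skills teaching, while also raising activity, could be reported as evidence that more active pupils behave better in class. This goes beyond detail that a condensed article may leave out, because the Outcomes section claims that the data can show what each component does. The design does not provide that, since all components arrive together.

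**Working it through.** **Layout.** The article gives six schools, 12 scans per school per term and 288 scans in total. The total is reproduced with four terms: 6 × 12 × 4 = 288, that is, 288 / (6 × 12) = 4. Four terms also fit one baseline term followed by three steps. (The description of the scans, read literally, gives 2 scans × 2 areas × 2 breaks × 3 days = 24 per term, not 12. That is a separate inconsistency; the layout here uses the stated 12 and 288.) This gives 6 × 4 = 24 school-term cells.

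**Assumptions, not in the article.** Two schools cross at each step, at terms 2, 3 and 4. Cells under intervention number 2×3 + 2×2 + 2×1 = 12, so the share is p = 12/24 = 0.5. Errors are independent, activity has no effect on behaviour, and the package shifts activity by dA and behaviour by dB, in standard deviations of cell values within condition.

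**Formula.** The correlation induced by a common binary cause is

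r = p(1−p)·dA·dB / √[(1 + p(1−p)·dA²)(1 + p(1−p)·dB²)]

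With p = 0.5 and dA = dB = d this becomes 0.25d² / (1 + 0.25d²).

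| dA | dB | Calculation | Induced r | Simulated share with two-sided p < 0.05 |
|---|---|---|---|---|
| 1 | 0 | 0 / √(1.25 × 1) | 0 | 4.9% |
| 0.5 | 0.5 | 0.0625 / 1.0625 | 0.06 | 5.6% |
| 1 | 0.5 | 0.125 / √(1.25 × 1.0625) | 0.11 | not simulated |
| 1 | 1 | 0.25 / 1.25 | 0.20 | 16% |
| 1.5 | 1.5 | 0.5625 / 1.5625 | 0.36 | 44% |
| 2 | 2 | 1 / 2 | 0.50 | 79% |

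The last column comes from 5,000 simulated trials per row. The first row shows that a shift in activity alone produces nothing; the second route to behaviour is needed.

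**After adjustment.** In the same simulations with intervention status held fixed, the mean correlation lay between −0.006 and 0.002 and rejection between 4.5% and 5.3%. With intervention status, school and term held fixed, the mean correlation lay between −0.005 and 0.006 and rejection between 4.6% and 5.1%. The induced correlation disappears.

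**The case against.** The strongest reply is that the article never says the correlation will be pooled over control and intervention periods. That is correct. The abstract offers one sentence, and the Background speaks of exploring trends. The plan to analyse all periods together concerns the playground observations, and it comes after analyses by school and by collection period. A reader might infer that pooling is specified; it is not. What stands is that no restriction or adjustment is named for a stated aim.

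A reader might also take the covariate list in Statistical methods as proof that intervention status is omitted from this analysis. It is not proof: those models relate the intervention to each outcome and do not describe the activity–behaviour analysis.

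Nor does the article credit behaviour change to activity alone. The Outcomes and Discussion sections name both routes, in the tentative form of what may happen and whether it will. Social skills may themselves come partly from active play, as the Background suggests, so the second route need not be wholly separate from activity.

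Finally, the effect sizes are assumed, as are the equal shifts and the 12/12 split. At half a standard deviation the distortion is slight, and the larger rejection rates need shifts of 1.5 to 2 standard deviations in both variables. To say that a spurious correlation will appear would overstate the case.

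These points limit the claim. They do not remove the common-cause structure, which the article itself describes, or the conflict between the Outcomes section and the end of the Discussion over separating components.

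**Conclusion.** The point holds in conditional form. An unadjusted activity–behaviour association taken over all periods is open to confounding by intervention status, and the article names nothing to prevent it. If the package shifts both variables equally, the induced correlation over 24 cells split 12/12 is about 0.06, 0.20 and 0.36 for shifts of 0.5, 1 and 1.5 cell-level standard deviations. It is zero if only one variable moves. The true size cannot be known from the article.

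The point concerns the interpretation of one stated aim and does not bear on the comparisons of intervention with control for each outcome. It is worth correcting because a plain correlation, carried out as announced, could mislead on that aim, and the remedy uses data already planned.

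**What to change.** - **Statistical methods:** state that the activity–behaviour association will be estimated at school-by-collection-point level, with intervention status and term in the model and school as the clustering effect. Label any unadjusted correlation, including the one announced in the abstract, as descriptive.
- **Outcomes:** remove the claim that the three data sets allow the effects of each component to be analysed separately, including the activity increase as against the social skills taught. This brings the section into line with the end of the Discussion.

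The cost is a few sentences and a small number of model terms, with no new data. The drawback is lower precision: adjustment sets aside the change in activity that the intervention itself creates and leaves an association over about 24 points. That association is still observational and open to other confounding within periods, for example by weather or supervision, both of which the playground scans record.

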**Trial Registration:**

Australian and New Zealand Clinical Trials Register ACTRN12616000575437, registered May 2016.

## Background

A multitude of evidence produced from research over the last decade in Australia clearly demonstrates the need for increased physical activity in primary school-aged children [1–3]. There are many health benefits from children being physically active, including greater cardiovascular fitness, lower systolic blood pressure and decreased risk of obesity [1]. Current research suggest that only about half of all Australian primary school aged children are meeting the National Physical Activity recommendations [4] guidelines of 60 min a day of moderate to vigorous physical activity (MVPA) [2].

As well as physical health, being physically active can have behavioural benefits for children, and these benefits to behaviour in primary school students are also becoming increasingly well evidenced [5, 6] and the importance of healthy eating and physical activity has been linked to positive behaviour in classrooms, increased on-task behaviour during class time, and higher levels of social competence [7–11]. The development of many social skills is another psychological benefit children can receive from participating in physical activity during unstructured play time (i.e. recess and lunch breaks. Pellegrini and Blatchford [12] found that social skills such as sharing, negotiation and conflict resolution were fostered through recess and lunchbreak activities.

The Healthy Active Peaceful Playgrounds for Youth (HAPPY) Study, aims to examine the relationship between physical activity and behaviour in primary school students, and to understand the environmental and societal factors that encourage physical activity in primary school students. Physical activity data will be collected before, during, and after the intervention to measure the impact that environmental modifications, social support and teacher training has on physical activity levels. This data collected on students behaviour will be gathered using a survey and direct observations in class time following breaks. Comparison of these data sets should allow for any trends between physical activity, and psychological well-being in students identified and explored.

The HAPPY Study has been designed with consideration to physical activity interventions that have been evaluated, and shown to improve physical activity levels [13, 14] and improve psychological well-being [15]. The HAPPY Study will evaluate how an intervention combining environmental modifications, teacher development, and peer support can culminate in an easy to implement, low cost and effective model for increasing physical activity, and improving psychological well-being for children.

## Methods/Design

### Study Design

The Healthy Active Peaceful Playgrounds for Youth (HAPPY) study is a 12 month, primary school-based intervention and will be evaluated using a cluster controlled trial with a stepped wedge design. Ethics approval has been obtained from an Australian University Human Ethics Committee (HREA5201500676) as well as from the New South Wales Department of Education and Communities (SERAP2015423). The HAPPY Study is registered with the Australian and New Zealand Clinical Trials Registry (ACTRN12616000575437). Principals, teachers and parents will provide written informed consent.

Following the recruitment process, data will be collected on students’ physical activity levels during lunch and recess, students’ on-task behaviour during class following lunch, and from whom the students receive social support from to be physically active. The intervention will be rolled out in a stepped wedge design. This means that all schools will start as ‘control’ schools and that the intervention will staggered across the 12-month period of the study (three steps in total) with data will being regularly collected across the period (Fig. 1). The stepped wedge design allows for an analysis of the interventions effectiveness and efficacy. As well as having the added benefit of ensuring all schools receive the intervention [16] (i.e., playground markings and teacher training). This benefit is often absent in classic Randomised Control Trials, where control groups may receive no immediate benefit from participating in research studies. This was the main rationale behind adopting this stepped wedge design.

